#### Analysis strategy

Randomisation is performed at primary care centre level and the results of the treatment will be analysed at individual patient level [13]. The analyses shall be per intent to treat.

First we will compare the intervention group with the control group in order to verify that there are no significant differences between the two groups (socio-demographic data, clinical baseline data, etc.). We shall use the mean (Standard Deviation) in the continuous variables and percentages in the categorical variables. For comparisons we shall use the Student-T test for continuous variables and the Chi-squared test for categorical variables. Non-parametric tests may also be used.

The main variables of the result are the depressive symptomatology (PHQ-9 score), response to treatment (reduction of 50% or more in the baseline score), remission (score of <5) and quality of life related to health (SF-12 score) at 3, 6 and 12 months.

Process variables include the number of visits for depression to the primary care centre, psychiatrist, emergencies and hospitalisations and the continued use of anti-depressants over 3 months.

We shall use the analysis of the linear mixed models of the SPSS v.15 statistical package, including the two effects, fixed and random, to analyse the effect of the continuous result variables (depression symptomatology [PHQ-9 score], quality of life related to health [SF-12 score]). We shall analyse the effect of the treatment on the categorical result variables (response and remission rates) by analysing the general linear models of the SPSS v.15. The random effects of these linear models (mixed and general) provide the structure that enables us to take into account the effect of randomisation by clusters owing to a potential lack of independence between observations within the same centre [33].

## Ethical aspects

The design of the study, with the random allocation of primary care centres to the control group or intervention group, makes it necessary to obtain informed consent on two levels: firstly, that of the participating doctors before they are allocated to the intervention or the control groups and, secondly, that of the participating patients, obviously once their centre has been allocated to the corresponding group, but before they are aware which group it is.

Before they give their consent, the patients are provided with a general overview of the aims and activities of the study. They are also informed that they will be participating voluntarily, and that they can choose to drop out at any time with the guarantee that they will continue to receive the treatment considered most appropriate by their doctor. The patients in the control group will receive the treatment considered most suitable by their doctor, without limitations.

The information provided to the health professionals is similar: participation in the study is voluntary and they can choose to drop out without any negative repercussions for the health or healthcare of their patients if they consider that continued participation will cause them harm. The participating professionals will sign a document in which they state that they will provide their patients with information, that they have no conflict of interest and that participation in the study favours the interests of their patients.

If the treatment evaluated proves to be effective, patients in all participating centres, including those in the control group, are guaranteed continued access to it. In this respect, the competent management authority will give their guarantee before the study begins and the centres are informed of it when their participation is requested.

The Study Protocol was approved by the Research Ethics Committee of the Jordi Gol i Gurina Primary Care Research Institute (IDIAP), Barcelona, on March 29, 2006 (ref: P06/16).

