### Setting and study sample

All of the 20 primary healthcare centres in the Tarragona-Reus Primary Care Area (Catalan Health Institute) in the province of Tarragona, Catalonia, Spain, have agreed to participate. The doctors from each centre who participated in the study had to be full-time employees, remain in the same location for the duration of the study and have a quota of patients assigned.

The doctors participating in the study will ask all patients who have suffered from an episode of major depression (DSM-IV) and who have been advised to take a new course of antidepressants to take part, until they reach their assigned quota of patients.

Patients considered for **inclusion **are those assigned to the doctor, aged ≥18 years, able to be contacted by telephone, who have been diagnosed with an episode of major depression (DSM-IV), have a score of >14 on the PHQ-9 (moderate-severe depression) or a score of 10 to 14 (mild depression) that has persisted for more than one month, and who have not received antidepressant medication in the previous three months.

The following patients will be **excluded**: those who suffer from physical, psychiatric or linguistic limitations or a concurrent illness that impede comprehension/participation in the study evaluations, patients with psychotic or bipolar disorders, patients with alcohol or drug dependence and patients who are pregnant or breastfeeding.

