### Allocation of study groups

In order to ensure comparability between the intervention group and the control group, each centre will be paired with another centre with similar features [13]: urban/rural location, the number of participating doctors and the availability of a psychiatrist in the own centre. One of each pair of centres will be randomly allocated as a treatment or a control centre. The pairing and the allocation will be carried out by an independent person not involved in the study.

The centres agree to participate before the random allocation. The patients agree to participate without knowing to which study group their centre has been allocated.

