### Control group (usual management)

The doctors in the centres that continue with standard treatment use their own criteria to attend depressed patients and are allowed to use any resources they consider appropriate, including referral to the specialised level. Although the activities involving the detection and diagnosis of the depression are not included in the evaluation, the doctors in the intervention group could become more aware through the diagnosis of the depression and detect cases with a milder depression, introducing an element of bias in the inclusion of patients. In order to prevent this, the doctors in the control group are given a training session on diagnosing and detecting depression, with the same content as that of the doctors in the intervention group.

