#### Variables and instruments of measurement (See Table 1)

**Table 1 T1:** Study variables

**Instrument**	**Assessment area**	**Applied by**	**Time(s) of assessments**
Sampling form	Age, sex, inclusion/exclusion criteria	Primary care physicians	Baseline
Sociodemographic data form	Age, sex, marital status, educational level, labour status, social class	Research interviewer by means of telephonic interview	Baseline
Duke Severity of Illness Checklist (DUSOI)	Global severity of physical comorbidity	Primary care physicians	Baseline
PRIME-MD; dysthymia and anxiety modules	Common psychiatric comorbidity	Primary care physicians	Baseline
Patient Health Questionnaire (PHQ-9)	Severity of depressive symptoms, remission and response rates	Research interviewer by means of telephone interview	Baseline, 3, 6 and 12 months
Questionnaire	Length of evolution of current depressive episode and previous history of depression.	Research interviewer by means of telephone interview	Baseline
SF-12 Health Survey	Health-related quality of life: mental health and physical health scores	Research interviewer by means of telephone interview	Baseline, 3, 6 and 12 months
Morisky-Green Test	Treatment adherence	Research interviewer by means of telephone interview	Baseline, 3, 6 and 12 months
Use of health resources questionnaire	Number of primary care, psychiatric and emergency visits, and hospitalisations owing to mental health problems	Research interviewer by means of telephone interview	3, 6 and 12 months
Satisfaction with the care received	Satisfaction of the patient with the clinical care got for his depression	Research interviewer by means of telephone interview	3, 6 and 12 months
Exploration of the computer database of pharmaceutical prescription and invoicing	Treatment with antidepressants. Medical prescription and consumption by the patient.	Research assistant	3, 6 and 12 months

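### Doctors who know their centre's arm recruit after allocation; giving control doctors the diagnostic session can reduce selection bias but cannot prevent it, and the planned analysis states no correction

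*Protocol article*

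**What the plan says.** **Timing and who is blind.** Under Ethical aspects, doctors consent first: "firstly, that of the participating doctors before they are allocated to the intervention or the control groups". Patients consent later, "obviously once their centre has been allocated to the corresponding group, but before they are aware which group it is". Allocation of study groups says the same: "The patients agree to participate without knowing to which study group their centre has been allocated". Apart from the patients, only the telephone interviewer is described as blind (Measurements).

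**Who recruits.** Setting and study sample gives the instruction: "The doctors participating in the study will ask all patients who have suffered from an episode of major depression (DSM-IV", limited to those "who have been advised to take a new course of antidepressants to take part, until they reach their assigned quota of patients". In Table 1, primary care physicians complete the sampling form, which covers "Age, sex, inclusion/exclusion criteria".

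**Training.** Intervention doctors have an 8-hour course covering diagnosis, suicidal risk, treatment, monitoring and a treatment algorithm, plus a toolkit and nurse case managers (Intervention). Control doctors have a session on diagnosis and detection with the same content on that topic. The Control group section gives the reason: intervention doctors might pick up milder depression, "introducing an element of bias in the inclusion of patients". It presents the session as the means to prevent this.

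**Analysis.** Analysis strategy compares baseline data by t test and chi-squared test to verify that the groups do not differ significantly. It names the outcome models but no covariates, and no consequence if a difference appears.

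**The concern.** Randomising and pairing centres balances centres. It does not balance the patients later enrolled by doctors who know what their centre will offer them. The protocol names this risk but treats it as a matter of diagnostic skill alone. Two other routes stay open:

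- A doctor with a new care programme may approach different patients from a doctor without one.
- A patient is invited only once advised to start an antidepressant. That is a treatment decision, and the trial trains doctors in treatment in one arm only.

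Remission at six months drives the sample size and is defined by an absolute threshold. If intervention patients start lower on the PHQ-9, more of them end below 5 whatever the programme does. A larger sample does not remove such a bias; it only estimates the wrong quantity more precisely.

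**Working it through.** **1. The plan's own figure.** Inputs from Sample size: 30% v 46% remission, two-sided alpha 0.05, power 80%, 15% loss, ICC 0.01, m = 20. With mean proportion 0.38:

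n = [1.960·√(2·0.38·0.62) + 0.842·√(0.30·0.70 + 0.46·0.54)]² / 0.16² = 143.3

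143.3/0.85 = 168.6, i.e. 169. Deff = 1 + 19·0.01 = 1.19, and 1.19·169 = 201. The stated figures reproduce. The concern is bias, so no new sample size follows from it.

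**2. What the remedy covers.**

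| Route to a different case mix | Equalised by the control session? |
|---|---|
| Skill in detecting and diagnosing depression | Yes |
| Decision to start an antidepressant (condition for invitation) | No; treatment training in one arm only |
| Knowledge of the arm when inviting and recording criteria | No |
| Compliance with the instruction to ask every eligible patient | No; no check is described |

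**3. Illustration of size.** These inputs are assumed and are not in the documents: baseline SD 4.5, follow-up SD 6, baseline-to-follow-up correlation r of 0.3 to 0.5, no treatment effect, normal scores with the threshold set so that control remission is 30% (z = −0.524). Intervention patients start d points lower.

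- Shift in follow-up mean = r·(6/4.5)·d; divide by 6 for SD units.
- Spurious remission = Φ(−0.524 + shift/6) − 0.30.
- 200·0.85 = 170 analysed per arm, 17 per centre, Deff = 1 + 16·0.01 = 1.16. SE = √(2·0.30·0.70·1.16/170) = 0.0535.
- Error from a noncentral t with 20 − 2 = 18 df (critical value 2.101), noncentrality = spurious remission/SE.

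For d = 1.5:

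| r | Shift (points) | Intervention remission | Spurious gain | Share of 16 points | Two-sided error |
|---|---|---|---|---|---|
| 0.3 | 0.6 | 33.6% | 3.6 | 22% | 9.7% |
| 0.4 | 0.8 | 34.8% | 4.8 | 30% | 13.5% |
| 0.5 | 1.0 | 36.0% | 6.0 | 38% | 18.7% |

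For d = 1 the error is 7.0 to 10.8%; for d = 2 it is 13.5 to 30.1%.

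**4. A second model.** Suppose a share of intervention patients are milder cases with higher remission. The spurious difference is share × (their remission − 30%).

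| Share | Their remission | Spurious difference | Two-sided error |
|---|---|---|---|
| 10% | 40% | 1 point | 5.4% |
| 20% | 50% | 4 points | 11.2% |
| 30% | 60% | 9 points | 36.1% |

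This uses an effective 201·0.85/1.19 = 143.6 per arm and a normal test.

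**5. Would the baseline tests settle it?** With the assumed SD of 4.5, 200 per arm and Deff 1.19, the SE of the baseline difference is 4.5·√(2·1.19/200) = 0.49. A true 1.5-point shift is 1.5/0.49 = 3.1 SEs and would usually be declared significant. A 1-point shift is 2.0 SEs, just under the critical 2.1, so it would be missed about half the time. In either case the test changes nothing in the outcome analysis.

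**The case against.** Several points on the other side stand.

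- **The recruitment rule is to ask everyone.** A reader might infer from "until they reach their assigned quota of patients" that doctors may choose whom to invite. The same sentence tells them to ask all eligible patients. The concern is that no check on this is described, not that the protocol grants discretion.
- **Entry is bounded.** It needs DSM-IV major depression, a PHQ-9 score above 14 (or 10 to 14 persisting more than a month), and no antidepressant in the previous three months. This limits how mild an enrolled patient can be, but leaves room for a shift within that range.
- **The blinded baseline PHQ-9.** A reader might infer that it has no role in entry. The article does not say which score decides eligibility. It says that physicians record the criteria and suggests that the interview follows inclusion.
- **Doctors' knowledge of the arm is inferred.** The inference is secure: they either have the course, toolkit and case managers or they do not.
- **Recruitment after allocation largely follows from the design.** Episodes are new and accrue over about 18 months, and the choice of clusters is justified in the Discussion. The timing is not itself an error.
- **The size is assumed.** In the first illustration the whole bias runs through baseline PHQ-9, so adjustment would essentially remove it. The figures apply only to an unadjusted analysis. The article does not say that the analysis is unadjusted, and covariates may be fixed in an analysis plan not shown.

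The last point does not rescue the claim of prevention, nor the reliance on baseline tests. Both are stated here.

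**Conclusion.** The point holds in limited form. Recruitment and the recording of entry criteria come after allocation and lie with doctors who in practice know their arm. The control session can reduce the bias that the protocol names, but cannot prevent it, because it leaves the treatment-dependent invitation and knowledge of the arm untouched. The baseline tests neither exclude nor correct a harmful imbalance.

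The documents do not show that the intervention arm will be milder, nor by how much; the protocol only raises the possibility. The range of about 4 to 6 spurious points and 10 to 19% error rests on an assumed 1.5-point shift, assumed SDs and correlations, and no baseline adjustment. It shows what a modest shift could do and is not an estimate for this trial. Correction is worthwhile mainly because the main remedy uses data already being collected.

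**What to change.** 1. In Analysis strategy, adjust the remission and PHQ-9 severity models for the baseline PHQ-9 taken by the blinded interviewer, in place of relying on baseline significance tests.
2. Pre-specify a sensitivity analysis restricted to patients whose blinded baseline score meets the PHQ-9 entry cut-off. Keep every enrolled patient in the main intent-to-treat analysis.
3. In the Control group section, say that the diagnostic session is given to reduce, not prevent, bias in inclusion.

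**Cost.** Slightly more analysis work and no new data.

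**Limits.** Adjustment does not remove bias from unmeasured differences such as cooperativeness. The article does not place the baseline call relative to the nurse's first visit at one week, so a late call could already reflect treatment. For that reason the blinded score is proposed as a covariate and for a sensitivity set, not as a gate to entry. Counting all new antidepressant starts on each doctor's list is not proposed either: it would draw on records of people who did not consent, and would not identify who met the DSM-IV and PHQ-9 criteria.

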## Forecast execution dates

Initial recruitment of patients: June 2007

Deadline for recruitment of patients: December 2008

Deadline for period of patient monitoring: December 2009

Publication of the results: March 2010

## Discussion

Previous experiences, particularly in the United States, have shown that the implementation of multifactorial programmes for the care of depression can give rise to better health results [10-12] and at present in several European health systems there are several research projects in progress that aim to investigate the usefulness of similar models for handling depression [34-36]. Along these lines, the objective of the INDI project is to create a programme for handling depression that can be applied in primary health care in the Spanish health system and to evaluate its effectiveness.

The intervention programme consists of an integral package of a variety of measures (organization for systematic and structured handling of depression, case management, professional training, clinical guidelines and treatment algorithm, psychological education of the patients) and one of its qualities is that it has been designed bearing in mind that it should be applicable to real caring practice so that, if the evaluation results are favourable, it can be easily generalized. The programme does not require considerable resources and the main aim of organizational measures is to optimize existing ones.

One of the innovative aspects, in our ambit, is to define and promote the role of the nurse in the systematic and structured handling of depression. The nurse is given the role of case manager and a central role in organizing the care of depressed patients. In an attempt to make the most of the resources available, it was decided to use the nurses already on the staff of the primary health care centre instead of contracting external case managers.

One of the limitations of our model is that it focuses on pharmacological treatment and does not consider psychotherapy as a front-line therapeutic option in primary care because in "real" caring practice in the Spanish health system it is a resource that is not often available and, although it would have been possible to include it in the context of a research project, it would be difficult to generalize in practice.

In the design of the clinical trial we opted to randomize clusters because the intervention to be evaluated is designed for primary health care centres (e.g. organizational measures) and health professionals (e.g. medical education) while the results of these interventions will be measured in individual patients in the form of health outcomes. This design makes it possible to avoid the attenuation of the effect of the intervention due to the possible contamination between study groups if the randomization were carried out individually and the patients assigned to the intervention and control groups were attended in the same place and even by the same professionals.

## Abbreviations

Deff, Design effect; DSM-IV, Diagnostic and Statistical Manual of Mental Disorders, Fourth Edition; DUSOI, Duke Severity of Illness Checklist; ICC, Intraclass coefficient correlation; IDIAP, Primary Care Research Institute (in Catalan: Institut D'Investigació en Atenció Primària); NICE, National Institute for Health and Clinical Excellence; PHQ-9, Patient Health Questionnaire; PRIME-MD, Primary Care Evaluation of Mental Disorders; SF-12, Medical Outcomes Study Health Survey, Short-Form, 12 items
